# Effects of an interactive mHealth innovation for early detection of patient-reported symptom distress with focus on participatory care: protocol for a study based on prospective, randomised, controlled trials in patients with prostate and breast cancer

**DOI:** 10.1186/s12885-017-3450-y

**Published:** 2017-07-04

**Keywords:** Information communications technology, mHealth, Application, Participatory care, Cancer supportive care, Cost-effectiveness, Study protocol, RCT, Clinical trial

## Abstract

**Background:**

Cancer patients are predominantly treated as out-patients and as they often experience difficult symptoms and side effects it is important to facilitate and improve patient-clinician communication to support symptom management and self-care. Although the number of projects within supportive cancer care evaluating mobile health is increasing, few evidence-based interventions are described in the literature and thus there is a need for good quality clinical studies with a randomised design and sufficient power to guide future implementations. An interactive information and communications technology platform, including a smartphone/computer tablet app for reporting symptoms during cancer treatment was created in collaboration with a company specialising in health care management. The aim of this paper is to evaluate the effects of using the platform for patients with breast cancer during neo adjuvant chemotherapy treatment and patients with locally advanced prostate cancer during curative radiotherapy treatment. The main hypothesis is that the use of the platform will improve clinical management, reduce costs, and promote safe and participatory care.

**Method:**

The study is a prospective, randomised, controlled trial for each patient group and it is based on repeated measurements. Patients are consecutively included and randomised. The intervention groups report symptoms via the app daily, during treatment and up to three weeks after end of treatment, as a complement to standard care. Patients in the control groups receive standard care alone. Outcomes targeted are symptom burden, quality of life, health literacy (capacity to understand and communicate health needs and promote healthy behaviours), disease progress and health care costs. Data will be collected before and after treatment by questionnaires, registers, medical records and biomarkers. Lastly, participants will be interviewed about participatory and meaningful care.

**Discussion:**

Results will generate knowledge to enhance understanding about how to develop person-centred care using mobile technology. Supporting patients’ involvement in their care to identify problems early, promotes more timely initiation of necessary treatment. This can benefit patients treated outside the hospital setting in regard to maintaining their safety.

**Clinical trial registration:**

June 12 2015 NCT02477137 (Prostate cancer**)** and June 12 2015 NCT02479607 (Breast cancer).

## Background

### Prostate and breast cancer patients’ needs

Prostate and breast cancer are currently among the most common cancer diagnoses worldwide [1] and the most common cancer diagnoses for men and women respectively in Sweden [2]. Due to developments in the treatment of prostate cancer, survival rates have improved [3, 4] but treatments come with a range of side effects, for instance urinary symptoms, bowel symptoms, pain, and fatigue, all of which affect patients’ quality of life (QoL) negatively [5–7]. Many of these symptoms can be long-lasting [7–9]. Likewise, advances in treatment have significantly improved breast cancer survival. Surgical excision of the tumour has generally been the first choice treatment but is increasingly being preceded by neo adjuvant systemic therapy. Similarly, this type of treatment regularly has side effects, including fatigue, dyspnoea, pain, nausea/vomiting, constipation and anxiety [10, 11], all of which impose substantial morbidity and burden on patients and their families and impact negatively on patients’ QoL, functioning and body image [12, 13].

Symptoms of cancer and side effects of treatment vary [14]; consequently, care and support should be based on the needs of the individual patient [7–9, 15]. Most patients in treatment remain living at home and this generally involves a degree of self-sufficiency in managing symptoms and side effects (self-care) including skills and knowledge concerning how to find and use information in regards to one’s health [16–18]. Currently, cancer patients may not receive adequate support to manage symptoms and side effects during treatment, resulting in a large number of patients visiting emergency departments, many of whom have to be hospitalised [19–23]. It has been concluded that self-care strategies are not a central focus for health care staff and patients [24–28] despite evidence that improvement in symptom management and self-care ability may lead to a faster return to daily activities and work [29, 30].

### Patient reported outcome measures (PROMs) and digitalization

Many cancer care providers have begun to incorporate patient-reported outcome measures (PROMs) into clinical practice, to support patients’ to be active in self-care and to identify when medical or nursing care interventions are needed [31–33]. A PROM includes any aspect of a patient’s health status (including disease symptoms, functioning and Health-related Quality of life-HRQoL) that is directly reported by the patient with no interpretation of the patient’s responses by a caregiver or anyone else [34]. Using PROMs in practice has been shown to improve patient-provider communication, facilitate early detection of problems, and to increase patient satisfaction [35–37]. For some time, it has been recognized that digital solutions can be of great assistance in these objectives [36, 38]. Therefore, evidence-based information and communication technology (ICT) which can contribute to early detection of symptoms and side effects within cancer care, is an urgent area for research, as this can aid prompt management, and increase patient safety and satisfaction.

### Mobile technology

Studies including technology for monitoring symptoms and providing self-care advice for cancer patients have been web-based [39, 40] or mobile -based [41]. The results show that interventions are user-friendly and feasible in clinical practice [41, 42] and increase patient-clinician communication [43]. The results also reveal effects, although small, on symptom management and symptom burden [40]. During the last decade there has been an increase in the number of scientific publications within the field of mobile health (mHealth) [44]. The vast majority concern the use of text messaging [44] but the use of apps is increasing, although research on its impact is scarce [45]. However, many apps focus on restricted aspects of the disease and hence risk failing to detect the multiple facets of the condition [45]. Moreover, apps have, among other issues, been criticized for lacking interactivity and for having content that is not relevant to users [44, 46]. Few studies exist on clinical outcomes and cost-effectiveness of using smartphone apps in health care [46].

### The development of an ICT platform - Interaktor

We have developed an ICT platform with an interactive app that takes into account the different needs patients may experience as they manage symptoms and concerns related to an illness. The platform is developed as part of a formal cooperation between the research group and a Swedish Company, Health Navigator (HN) specialising in health care management. Interaktor includes a web interface and an app that is downloaded onto a smartphone or a tablet. The components are: 1) patients’ assessment of the occurrence, frequency and distress level of symptoms, 2) a web interface for the healthcare providers, for monitoring patients’ data in real time, 3) an alert function, based on a risk assessment model, which sends alerts to the nurses via text message (SMS), 4) access to evidence-based self-care advice related to symptoms and links to relevant websites, 5) graphs of symptom report history. The web interface functions both as an aid in patient-clinician communication about symptoms and self-care and as a decision aid for health care personnel managing symptoms. The reported data is stored at a designated secure server at HN (Fig. 1).

**Fig. 1 Fig1:**
[figure not shown]
Illustration of the ICT-platform

Development was guided by the framework of The Medical Research Council (MRC) [47] which recommend that complex interventions should be developed, tested and implemented in a process that encompasses three stepwise phases: i) defining and understanding the problem and the context; ii) developing the intervention and; iii) developing and optimizing the evaluation. The design and content of the app is based on the results of literature reviews and produced in a collaborative effort with patients and health care staff.

### Aim and hypothesis

This study aims to evaluate the effects of the interactive ICT platform (Interaktor) developed for this project, on patients with breast cancer during neo adjuvant chemotherapy treatment and patients with locally advanced prostate cancer during treatment with radiotherapy respectively. The main hypothesis is that the use of the platform will improve clinical management, reduce costs and promote safe and participatory care. Furthermore, the study population enables investigation of whether the intervention effects are generic. The specific research questions are:Will using the app during treatment for breast and prostate cancer respectively:
Minimize symptom burden?Enhance participatory and meaningful care?Improve the capacity to access, understand, communicate and use health information for health promoting behaviours?Impact the QoL positively, or affect disease progress and health care costs?
2.How does a person’s inner strength (sense of coherence) influence intervention effects?3.How feasible, user-friendly and accepted is the platform according to patients and health professionals?4.Are there any differences in study outcomes regarding diagnosis?

## Design and methods

The study has a prospective, repeated measure RCT design including patients with breast cancer during neo adjuvant chemotherapy treatment and patients with locally advanced prostate cancer during radiotherapy.

### Prostate cancer study

Data are collected during 20 weeks, at three time points; baseline, end of treatment and three months after the end of treatment, see SPIRIT study flow chart in Fig. 2. Patients are recruited from two clinics in Stockholm County Council in Sweden; the Department of Oncology at Karolinska University Hospital and the Department of Oncology Södersjukhuset. Recruitment began in August 2015 and completion for recruitment is expected in August 2017. A sample of 150 prostate cancer patients will be recruited. Inclusion criteria are; patients diagnosed with prostate cancer, scheduled to receive curative radiotherapy for at least five weeks. Exclusion criteria are: inability to read or understand Swedish, or having a known severe cognitive disability. Patients scheduled for radiotherapy are consecutively identified for eligibility by one of the researchers by screening of the booking lists. Eligible patients are sent a letter with information about the study and contacted by one of the researchers via telephone approximately a week before their first treatment appointment. Those who agree to participate sign a consent form and fill out the baseline assessment questionnaire before being assigned to either the intervention or control group by a sequence of sealed envelopes with equal distribution among the two groups [48].

**Fig. 2 Fig2:**
[figure not shown]
SPIRIT flow chart RCT-study prostate cancer

#### Intervention and standard care

All patients receive standard treatment and care according to clinical guidelines and the protocol of the clinic where they are treated. This includes radiotherapy five days a week, with or without a combination of two sequences of brachytherapy, and regular contact with an assigned oncology contact nurse who can be contacted during office hours. The patients in the intervention group download the app onto their own smartphone or tablet; alternatively they may borrow such a device from the research group. They are instructed on how to use the app for reporting symptoms and start reporting in the app on their first day of radiotherapy. They then report daily, during weekdays, and three weeks following the last treatment. The total time for reporting is between eight to 11 weeks depending on whether the treatment is a combination treatment or not. The nurses at the clinic receive instructions and training on how to use the platform, including the alert system, and how to monitor the patients´ reports. Reporting in the app is a complement to the usual care and patients are encouraged to report before 3 PM as reports and alerts are managed during office hours (7 AM-4 PM). If emergency health care attention is needed the patients are instructed to contact the health care according to the standard procedure at the oncological clinic.

#### The prostate cancer version of Interaktor

The prostate cancer version includes 14 symptom questions regarding bladder and bowel function, fatigue, pain, worry, depression, sleep, and flushing. They are included as a result of a literature review, interviews with patients and healthcare providers [25] and a feasibility study [49]. Furthermore, there is an open question, providing the patient with an opportunity to add comments; *“Other symptoms or concerns to report?”* Patients are asked about the symptoms’ occurrence, frequency, and distress level during the day, for example: *“Do you experience urinary difficulties?”* If the answer is yes, the patient is asked about the frequency, which can be rated as: almost never, sometimes, rather often, or very often. Next follows a question on distress level, which can be rated as: not at all, a little, somewhat, or very much. The symptoms of fatigue, insomnia, constipation and blood in stool are only assessed by the distress level and not by frequency. Specific symptoms are set to generate an alert to the registered nurses, via text messages (SMS), on appointed levels of frequency or distress. The level for each symptom has been decided based on a risk assessment model, in collaboration with clinicians. There are two kinds of alerts: yellow alerts that request a nurse to contact the patient during the day, and red alerts, requiring contact within one hour. Severe symptoms regarded as a potential risk for the patients’ health and well-being trigger a red alert. A symptom considered to be less severe triggers a yellow alert. The symptoms set to trigger alerts are: urinary urgency (very often; yellow alert), difficulties urinating (very often; red alert), haematuria (very often; yellow alert), diarrhoea (very often; yellow alert), blood in stool (very much; red alert), obstipation (very much; yellow alert), pain (very often; red alert) and depression, worry (very often; red alert).

### Breast cancer study

Data are collected over 30 weeks, at three time points; baseline, end of treatment and three months after the end of treatment, see SPIRIT study flow chart in Fig. 3. Patients are recruited from two clinics in Stockholm County Council in Sweden; the Department of Oncology at Karolinska University Hospital and the Department of Oncology Södersjukhuset. Recruitment began in June 2015 and is expected to be complete in June 2017. A sample of 150 breast cancer patients will be recruited. Inclusion criteria are: patients with breast cancer receiving neo adjuvant chemotherapy, men or women, 18 years or older. Exclusion criteria are: unable to read and understand Swedish, or patients with a known severe cognitive disability. Eligible patients are consecutively identified by one of the researchers through screening of booking lists and are provided with written information by the assigned oncology nurse or physician during their first visit. The patients who approve to be contacted by the researcher are called and a meeting is arranged. The patients consent to participate in the study by signing a consent form and after that fill in the baseline assessment questionnaire before being randomised to either the intervention or the control group by a sequence of sealed envelopes with equal distribution among the two groups [48].

**Fig. 3 Fig3:**
[figure not shown]
SPIRIT flow chart RCT-study breast cancer

#### Intervention and standard care

All patients receive standard treatment and care according to clinical guidelines and the protocol of the clinic where they are treated. Standard treatment and care consist of neo adjuvant chemotherapy and regular visits to the physician and the oncology contact nurse prior to every treatment occasion. The patients in the intervention group download the app onto their own smartphone or tablet; alternatively they may borrow such a device from the research group. They are instructed on how to use the app for reporting symptoms and start reporting in the app on their first day of chemotherapy. They then report daily, during weekdays, and two weeks following the last treatment, alternatively until the day of surgery. The total reporting time is approximately 18 weeks. Reporting in the app is complementary to the usual care and patients are encouraged to report before 3 PM as the reports and alerts are managed during office hours (7 AM- 4 PM). If emergency health care attention is needed the patients are instructed to contact the health care according to the standard procedure at the oncological clinic.

#### The breast cancer version of Interaktor

The breast cancer version includes 14 symptom questions regarding fever, breathing difficulties, pain, nausea, vomiting, bowel function, oral problems, worry, depression, fatigue, insomnia, numbness/tingling in the hands and feet, and pain/swelling/redness in the arm (relating to the peripherally inserted central catheter line for chemotherapy administration). Furthermore, there is an open question providing the patient with an opportunity to add comments; *“Other symptoms or concerns to report?”* The questions were formulated based on extant literature and guidelines and subsequently pilot-tested on eight patients. Results from the feasibility study of the prostate cancer version were considered sufficient and thus no feasibility study was conducted for the breast cancer version. Patients are asked about the symptoms’ occurrence, frequency, and distress level during the day, for example: *“Do you experience nausea?”* If the answer is yes, the patient is asked about the frequency, which can be rated as: never, sometimes, rather often, or very often. Next follows a question on distress level, which can be rated as: not at all, a little, somewhat, or very much. The symptoms fever and pain/swelling/redness in the arm are only assessed by occurrence. The symptoms constipation, oral problems, worry, distress and insomnia are only assessed by the distress level and not frequency. Specific symptoms are set to generate an alert to the registered nurses via text messages (SMS) triggered by either occurrence, frequency or distress level. The level for each symptom was decided based on a risk assessment model, in collaboration with clinicians. There are two kinds of alerts: yellow alerts that request a nurse to contact the patient during the day, and red alerts, requiring contact within one hour. Severe symptoms regarded as a potential risk for the patients’ health and well-being trigger a red alert. A symptom considered to be less severe generates a yellow alert. The symptoms set to generate alerts are: fever (yes; red alert), pain/swelling/redness in the arm (yes; yellow alert) breathing difficulties, nausea and vomiting (rather often; yellow alert, very often; red alert) diarrhoea (very often; yellow alert), obstipation and worry (very distressing; yellow alert) and lastly oral problems (somewhat distressing; yellow alert).

### Primary outcomes

#### Questionnaires

Outcomes concerning HRQoL, symptom distress, perception of individual care, sense of coherence and health literacy will be collected through validated self-report questionnaires;EORTC-QLC-C30 (including disease-specific module PR-25 in the prostate study) for the evaluation of HRQoL [50].The Memorial Symptom Assessment Scale (MSAS) a 32-item questionnaire for measuring symptom prevalence, characteristics and distress (Breast cancer study only) [51].The Individual Care scale (ICS): a 24-item self-measurement of perception of individual care [52].The Sense of Coherence Scale a 13-item questionnaire for measuring overall coping ability (inner strength) [53, 54].The Health literacy scale: a ten-item questionnaire assessing functional, communicative and critical health literacy [55].

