#### Registers and logged data

Medical data (morbidity, mortality, recurrence rate, biomarkers) will be obtained from medical journals, and socioeconomic data and health care costs (visits, pharmaceuticals) will be collected from medical registers up to six months after the intervention for a cost-effectiveness analysis of the intervention. Logged data on symptom reports and self-care advice accessed (adherence to the intervention) including frequencies of symptoms and generated alerts will be collected.

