### Sample size calculation

The sample size is estimated from the results of the effect study including patients with prostate cancer, Sundberg et al. [56] With an effect size (Cohen’s d) difference of 0.54 in the primary outcome (urinary symptom) with 90% power at *p* < 0.05, 71 patients in each group are needed. A similar study with an expected effect size (Cohen’s d) difference of 0.20 in the primary outcome (symptom improvement) with 85% power at *p* < 0.05 with five repeated measurement needed 133 patients in each group [40]

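### Every outcome stands under a primary label while the sizing uses one urinary symptom outcome, so the stated 0.05 and 90% power attach to no defined primary claim

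*Protocol article*

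**What the plan says.** All outcomes in the protocol article fall under one heading, "Primary outcomes". No secondary or exploratory heading follows. Beneath it stand:

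- Questionnaires: "Outcomes concerning HRQoL, symptom distress, perception of individual care, sense of coherence and health literacy will be collected through validated self-report questionnaires". The instruments are the EORTC C30 (with the PR-25 module in the prostate study), the MSAS (breast study only), the Individual Care scale, the Sense of Coherence scale and a health literacy scale.
- Registers and logged data: "Medical data (morbidity, mortality, recurrence rate, biomarkers) will be obtained from medical journals"; "health care costs (visits, pharmaceuticals) will be collected from medical registers up to six months after the intervention"; and "Logged data on symptom reports and self-care advice accessed (adherence to the intervention) including frequencies of symptoms and generated alerts will be collected".
- Feasibility interviews with intervention-arm patients, and interviews on participatory and meaningful care with 80 patients from both arms.

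The section Sample size calculation uses one outcome, a "difference of 0.54 in the primary outcome (urinary symptom) with 90% power", at p < 0.05, giving 71 per group. The effect size comes from an earlier study in prostate cancer. Each trial recruits 150 patients.

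Under Aim and hypothesis, "The main hypothesis is that the use of the platform will improve clinical management, reduce costs and promote safe and participatory care". Research question 2 in the same section asks how a person's "inner strength (sense of coherence) influence intervention effects". The section Statistical analysis plans linear mixed-effect models for repeated measurements and does not say which outcome is primary.

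**The concern.** A sample size, a significance level and a power figure mean something only for a named comparison. Here the outcome section makes everything primary and the sizing section makes one thing primary. The sizing sentence can be read in two ways, and neither helps. If urinary symptom is this study's primary outcome, that contradicts the outcome section, which never singles it out. If it is only the earlier study's primary outcome, this study names none.

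The breast trial is worse placed. Its sizing outcome was observed in prostate patients, and PR-25, the prostate-specific module, is not given to breast patients.

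At stake is how a result may be reported. With no hierarchy, a significant difference on any listed scale could be presented as a positive primary outcome. Sense of coherence also has two roles that do not fit together: a listed outcome, and a modifier of the effect in research question 2.

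**Working it through.** **1. Reproduce the stated sample size.** Inputs from Sample size calculation: d = 0.54, power 90%, alpha 0.05. Two-sided testing is assumed, since the article does not state it. Allocation is equal.

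n per group = 2(z₀.₉₇₅ + z₀.₉₀)² / d² = 2(1.960 + 1.282)² / 0.54² ≈ 72.1, rounded up to 73.

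The article states 71, which is within two patients; an unrounded d of about 0.545 gives 71. One-sided testing gives 59 and does not reproduce it. The figure therefore corresponds to one two-sided test at 0.05, with no allowance for several primary outcomes.

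**2. Does the paragraph size the breast trial in some other way?** It also mentions a similar study with d = 0.20 that needed 133 per group, or 266 in total. Neither trial adopts that figure. The target of 150 (75 per group) fits 2 × 71 = 142. The breast trial thus takes its size from the prostate outcome.

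**3. Count the outcomes that can be compared between arms.** This count is an assumption, because the article does not fix it.

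- Questionnaires, breast: C30, MSAS, individual care, sense of coherence, health literacy = 5. Prostate: the same with PR-25 in place of MSAS = 5, or 4 if PR-25 is counted as part of C30.
- Registers: morbidity, mortality, recurrence, biomarkers, costs = 5.
- App logs and feasibility interviews exist only in the intervention arm, and both interview sets are qualitative. They add no between-arm tests.

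**4. Chance of at least one false positive if each were tested at 0.05.** Under independence this is 1 − 0.95^k. For k = 5, 1 − 0.774 = 22.6%. For k = 10, 1 − 0.599 = 40.1%. The correlated values come from simulating equally correlated normal test statistics (400,000 replicates).

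| Outcomes tested | Independent | Correlation 0.5 | Correlation 0.7 |
|---|---|---|---|
| 4 (questionnaires without sense of coherence) | 18.5% | 15.6% | 13.1% |
| 5 (questionnaires) | 22.6% | 18.3% | 14.8% |
| 10 (questionnaires and registers) | 40.1% | 28.7% | 21.3% |

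**5. What each way out would need,** at d = 0.54 and 90% power:

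- One named primary outcome: 73 per group. With 75 per group, power is Φ(0.54 × √(75/2) − 1.960) = Φ(1.347) = 91.1%.
- Five co-primary outcomes with Bonferroni (alpha 0.01 each): 103 per group; 75 per group give 76.8% for each outcome.
- Ten co-primary outcomes (alpha 0.005 each): 115 per group; 75 per group give 69.1%.

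The planned 150 patients therefore fit one primary outcome and not several.

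**The case against.** The strongest reply is that this is a condensed article. A multiplicity rule commonly belongs in an analysis plan, a consultant statistician is to take part in the analyses, and two registrations are cited that are not at hand. That stands as far as it goes: the absence of a stated correction is not the finding. But the article does not simply leave the hierarchy out. It labels all outcomes primary and then sizes on one, and an analysis plan would still have to resolve that.

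Some stronger readings are tempting and are not supported:

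- *All tests will be run uncorrected at 0.05.* That level appears only in the sample size section; the analysis section states none.
- *Twenty or thirty tests, with error rates of 64% or 79%.* Those figures treat repeated visits or subscales as independent tests, whereas mixed models for repeated measurements are planned.
- *Logs and interviews multiply the tests.* They permit no between-arm significance test.
- *A urinary outcome lies outside the study's aims.* The main hypothesis does not name it, but the first research question asks about symptom burden, and the abstract lists symptom burden first among its outcomes.
- *The sense-of-coherence analysis will be biased.* That would follow only if post-randomisation values were used as the modifier, and nothing says they will be.
- *The study was sized on the PR-25 urinary scale.* The sizing section names no instrument.

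**Conclusion.** The concern holds as a contradiction within the document. One section designates every outcome primary, another sizes on a single urinary symptom outcome, and neither yields to the other. The breast trial borrows a size derived for a prostate outcome. As a result, the stated 0.05 and 90% power describe no defined primary claim in either trial.

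If every between-arm outcome were tested at 0.05, the false-positive chance would be about 15–23% for five outcomes and 21–40% for ten, roughly three to eight times nominal. This rests on assumed test counts, on equal correlations between 0.7 and 0, and on no correction being applied. It shows what the labelling would permit and does not predict what the analysts will do. The double role of sense of coherence is a separate, smaller inconsistency under the same heading.

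**What to change.** Before the data are analysed, and for each trial separately:

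- Name one primary scale and one primary time point, or one overall contrast from the mixed model.
- Prostate: use the urinary symptom score that matches the sizing outcome. The PR-25 urinary scale is a candidate, to be confirmed against the earlier study.
- Breast: use one pre-specified symptom-distress score, for example from the MSAS. State that the 90% power was derived for the prostate urinary outcome only.
- Relabel the remaining questionnaires, clinical events and costs as secondary with Holm adjustment, or as exploratory.
- Move app logs and interviews to a process evaluation.
- Take sense of coherence off the outcome list and analyse it as a baseline-score-by-arm interaction.

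The cost is protocol or analysis plan wording and a registry update, with no new data and no change to the 150 patients per trial. The downside is that the other scales lose primary status. If several co-primary outcomes are preferred, the alpha must be divided and the sample enlarged, as the Bonferroni figures above show.
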